### MODN

In parallel with the MIRT-based development, AfriCAT will also be implemented using a MODN architecture [27]. MODN is a modular neural network framework in which each symptom question functions as an independent module that updates diagnostic probability estimates sequentially as new information is obtained [27]. Rather than estimating a single latent trait, this approach models the evolving probability of specific diagnostic states, recalibrating predictions dynamically with each response. Unlike traditional latent trait models, MODN more closely mirrors the logic of a clinical consultation, in which information is gathered iteratively and diagnostic impressions are updated in real time.

A deep learning encoder module will be created for each question in the dataset. A deep learning decoder module will be created for each outcome. Missing data are accommodated by the modular architecture and are simply ignored.

Five-fold cross-validation will be performed on the training set to optimize the hyperparameters of the models. The final models will then be trained on the full training set with the optimal hyperparameters. All analyses will be performed using the trained models on the test set. Overfitting will be controlled by early stopping the training after increases in the validation loss and sanity-checking the loss curves.

To remedy the low prevalence of internalizing disorders, we will also train models that overweight positive diagnosis cases. As the survey weights do not substantially alter the prevalence of the internalizing disorders, the models trained using them are not expected to differ significantly and would be less representative of individual adolescents. We will therefore not use the survey weights.

The model achieving the best prediction performance using all the questions on the test set will then be selected. Different combinations of next-question-selection methods and stopping rules will be compared based on their predictive performance and efficiency. They will be compared against baselines using entropy-based methods as next-question-selection and the *DISC-5* diagnostic criteria satisfaction as the stopping rule.

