### MIRT-Based CAT Development

To capture the latent structure of symptoms appropriately, a bifactor multidimensional framework is outright adopted for model calibration. Within this definitive framework, all items load directly onto a single general internalizing factor while simultaneously contributing to independent, disorder-specific factors corresponding to MDD, GAD, SoPh, and PTSD. Model fit for this bifactor configuration will be rigorously assessed by evaluating the strength and significance of item factor loadings, examining global fit statistics, specifically the limited-information M2 statistic alongside absolute and relative indices such as the root mean square error of approximation and the comparative fit index, and visually inspecting observed versus expected item response plots to identify localized areas of measurement.

*DISC-5* symptom items in the K-NAMHS dataset are recorded as binary (yes/no) responses, indicating the presence or absence of specific symptoms. Item parameters will therefore be estimated using dichotomous item response theory models, allowing estimation of item discrimination and severity parameters for each symptom indicator. The baseline MIRT bifactor calibration will be executed via a stochastic expectation-maximization algorithm. To ensure population representativeness, normalized complex survey weights will be integrated directly into the estimation process to scale individual contributions to the marginal likelihood. Missing data handling strategies will differ by analytical phase. For the core MIRT calibration, missingness will be accommodated via full-information maximum likelihood, which leverages all available structural information without data loss. However, because post hoc adaptive testing simulations within the MIRT-CAT framework require a complete matrix to execute through high-missingness skip patterns, model-based plausible value imputation will be utilized strictly to construct the complete simulation response bank.

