### Outcomes

#### Primary Outcomes

Because MIRT and MODN estimate fundamentally different quantities, namely severity and probability of diagnosis, they cannot be meaningfully compared head-to-head. Instead, we will review the relative strengths and limitations of the models in supporting measurement-based mental health care. Primary metrics of evaluation will include (1) precision of severity estimation across internalizing symptom dimensions; (2) efficiency, operationalized as the median number of items required to achieve stable estimates or certain predictive performance; and (3) diagnostic classification performance relative to *DSM-5* diagnoses for MDD, GAD, SoPh, and PTSD. Diagnostic classification performance will be evaluated using established metrics such as sensitivity, specificity, and area under the receiver operating characteristic curve. To assess fairness across age and gender, each outcome will be computed for each subgroup and compared.

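### MODN is to ignore missing answers although skip patterns cause much of the DISC-5 missingness, so its simulated comparison of selection rules may be biased in either direction

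*Protocol article*

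**What the plan says.** The MODN section builds the network from separate question modules: "A deep learning encoder module will be created for each question in the dataset". On missing answers it gives one rule: "Missing data are accommodated by the modular architecture and are simply ignored". It then plans the adaptive evaluation: "Different combinations of next-question-selection methods and stopping rules will be compared based on their predictive performance and efficiency". On the reference methods it adds: "They will be compared against baselines using entropy-based methods as next-question-selection". The section gives no skip code, gate-order constraint or completed data set for MODN.

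The section on MIRT-Based CAT Development treats the same item bank differently. It says the adaptive simulations "require a complete matrix to execute through high-missingness skip patterns", and that "model-based plausible value imputation will be utilized strictly to construct the complete simulation response bank". That completed bank is described only for the MIRT engine.

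Under Primary Outcomes, efficiency is "the median number of items required to achieve stable estimates or certain predictive performance", and a further primary metric is "diagnostic classification performance relative to" DSM-5 diagnoses. According to Data Source, those diagnoses come from the DISC-5 scoring algorithms, and so from the same interview.

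**The concern.** A skip pattern means that an earlier answer (the gate) decided whether a follow-up was asked. Missingness of that kind depends on the respondent's answers and, since the diagnosis is scored from the same interview, on the outcome. Ignoring it has two consequences.

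- **Training.** A follow-up's encoder can learn only from adolescents who were asked the item. Either answer, including a no, is therefore learned among those whose gate was open. This holds however the simulator later treats skipped items.
- **Replay.** A selection method may pick a follow-up for which an adolescent has no recorded answer. If such items are removed from the eligible set, the set itself reveals a gate answer that was never asked or counted. If they are counted with no update, the simulation spends a question that a live respondent would have answered.

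At stake are the ranking of selection methods and stopping rules in the MODN section and the item counts and accuracy under Primary Outcomes. Both feed prototype design. The 20% held-out set cannot expose the problem, because it carries the same skip patterns.

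**Working it through.** The document states no performance figure, gate rate or per-item missingness, so there is no figure to reproduce. Two checks were made, both on assumed settings.

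**1. How much gate information item availability could carry.** Assume a diagnosis requires an open gate, prevalence d and gate endorsement g. Classifying only by whether follow-ups were recorded gives sensitivity 1, specificity (1 − g)/(1 − d) and AUC (1 + specificity)/2.

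| d | g | Specificity | AUC |
|---|---|---|---|
| 0.05 | 0.10 | 0.90/0.95 = 0.947 | 0.97 |
| 0.05 | 0.25 | 0.75/0.95 = 0.789 | 0.89 |
| 0.05 | 0.40 | 0.60/0.95 = 0.632 | 0.82 |
| 0.02 | 0.10 | 0.90/0.98 = 0.918 | 0.96 |
| 0.02 | 0.25 | 0.75/0.98 = 0.765 | 0.88 |
| 0.02 | 0.40 | 0.60/0.98 = 0.612 | 0.81 |

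These values show what could leak. They do not measure bias, because a live test obtains the same information by asking the gate and counting it.

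**2. What the handling of skipped items does to the replay.** Settings, all assumed:

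- four disorders, each with one gate and eight binary follow-ups from a bifactor trait;
- follow-ups recorded only if the gate is yes;
- diagnosis if the gate is yes and at least four of eight follow-ups are yes;
- 60,000 training and 60,000 test records;
- a logistic sequential scorer standing in for MODN, with no update for a missing answer.

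Three gate severities gave target-disorder prevalence of 14.6%, 11.6% and 7.7%, with 58%, 69% and 77% of the bank missing. The table shows the difference in AUC from a gate-respecting rule (follow-up eligible only after its gate was asked and answered yes) for these three scenarios in that order.

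| Question order | Questions | Answered items only | Skipped item counted, no update |
|---|---|---|---|
| Random | 1 | +0.011, +0.048, +0.080 | −0.171, −0.171, −0.171 |
| Random | 3 | +0.021, +0.025, +0.024 | −0.156, −0.183, −0.208 |
| Follow-ups first | 1 | +0.035, +0.011, +0.002 | −0.013, −0.053, −0.066 |
| Follow-ups first | 3 | +0.016, +0.008, +0.004 | −0.018, −0.031, −0.032 |
| Most informative first | 1 to 12 | 0 | 0 |

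For example, the largest gain is 0.844 − 0.764 = 0.080, and the largest loss at three random questions is 0.723 − 0.931 = −0.208. A higher AUC at a given length means a performance target is reached with fewer items, so the item count shifts in the same favourable or unfavourable direction.

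Availability alone gave AUC 0.879, 0.938 and 0.973 in the three scenarios. One counted question under most-informative-first selection gave the same values, which is consistent with the gate being picked first. This supports reading the AUCs in check 1 as the gate's own discrimination.

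With every item answered, three random questions gave AUC 0.784, 0.786 and 0.783, against 0.853, 0.892 and 0.931 with gates respected. A completed bank therefore evaluates a different test, in which follow-up modules meet respondents unlike those they were trained on.

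**The case against.** The strongest reply is that the ignored-missingness sentence describes the architecture, and that a condensed article may leave the simulator's handling of skipped items to a fuller document. Nothing excludes gate-ordered selection. MODN is likened to a consultation that gathers information step by step, and the prototype is to present items according to earlier answers. The article names no gate items and gives no missing share. Prototypes are for research only, external validation is to follow, and the limitations concede that simulation cannot replace field testing.

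Much of this stands. A reader might infer that MODN's efficiency and accuracy are inflated. The document does not support that: it never says selection is limited to answered items, and the other handling gives a loss, or no difference when the most informative item comes first. A reader might also take AUCs of 0.81 to 0.97 as the amount of inflation, but they are largely legitimate gate information under assumed rates. Nor does the document say that the prototype would ask follow-ups without their gates.

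What does not stand is that this is merely omitted detail. The article states a rule for MODN missingness without separating skips from non-response, and for the other engine it treats the same skip patterns as needing special handling.

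**Conclusion.** The point holds as a risk of bias whose direction is open. Ignoring structural skips means that gated follow-up modules are trained on a selected group. The replay is then optimistic if selection is limited to answered items, can be pessimistic if skipped items are counted with no update, and shows little or no bias if gates come first. Because the effect differs by selection rule, it can distort the comparison the MODN section is meant to make, as well as the primary efficiency and classification metrics.

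In the illustration, answered-only selection gained at most 0.08 in AUC after one question. Counting skipped items lost 0.16 to 0.21 after three random questions. These figures rest on an assumed gate structure, prevalence, scorer and question order. The actual size cannot be computed from the document. The change is cheap and still timely, since the Results section places simulation-based validation after model calibration, which is under way.

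**What to change.** In the MODN section, separate structural skips from true item non-response and ignore only the latter. For skips, add an eligibility rule:

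- a follow-up may be selected only after its gate item has been asked in the same simulated session and answered in the direction that opens it;
- the gate item counts toward test length;
- the rule applies to the question order used in training, to all selection methods and to the baselines.

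As a sensitivity analysis, repeat the comparison on the completed response bank already planned for MIRT, bearing in mind that its filled-in answers come from a model. Report the AUC from item availability alone as a leakage check, labelled as the information that could leak and not as the bias.

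The cost is coding the skip map into the simulator and training loop, and a possibly longer reported test. No new data are needed.

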### Conceptual Framework

The AfriCAT study was designed to address these gaps by developing a computerized adaptive assessment for depression and anxiety among adolescents using nationally representative data from Kenya. Importantly, AfriCAT is conceptualized not as a screening tool alone but as a scalable adaptive assessment engine embedded within a stepped-care system to support measurement-based mental health care.

Within this framework (Figure 1), adaptive assessment contributes to 3 core functions across the care pathway. First, it supports identification by estimating the probability of depressive and anxiety disorders and generating dimensional severity scores. Second, these outputs inform triage, enabling stratification of individuals into levels of care based on symptom severity and risk, ranging from low-intensity, high-volume interventions to more intensive, clinician-supported services. Third, repeated adaptive assessments enable measurement-based care, allowing providers to monitor symptom trajectories and adjust treatment through step-up or step-down transitions over time.

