### Prototype Development

Insights from both the MIRT- and MODN-based approaches will inform final prototype design, including the possibility of hybrid architectures that combine strengths of probabilistic prediction and latent severity estimation. Two complementary user interfaces will be developed to reflect the different contexts in which AfriCAT may be used within measurement-based mental health care systems.

The first is an adolescent-facing interface designed for self-administration, for example, via smartphone or tablet in school, community, or clinic settings. This version will deliver symptom questions adaptively, presenting items sequentially based on prior responses to minimize burden while maintaining precision. Upon completion, the tool will provide structured feedback tailored to symptom severity alongside guidance regarding appropriate referral or support options.

The second interface is a provider-facing version intended for use by primary health care workers, mental health professionals, or trained lay providers within task-shared systems of care. In this format, the adaptive assessment will be designed for integration into the clinical encounter, supporting real-time evaluation of symptom severity. The tool will be designed to generate dimensional severity estimates and probabilistic diagnostic outputs that can inform clinical decision-making. The prototypes developed during this study are intended for research and feasibility testing only and will not be used to make independent clinical decisions or provide automated crisis management recommendations.

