#### Secondary Outcomes

Secondary outcomes include evaluation of the adaptive assessment’s ability to estimate a general internalizing dimension alongside disorder-specific symptom domains, as well as assessment of model stability under internal validation procedures. For the MODN architecture, the calibration of probabilistic outputs will be assessed using calibration curves and the expected calibration error metric. The interpretability of sequential prediction updates will be represented as heatmaps and will be qualitatively assessed for potential integration into routine provider workflow.

For the DCE, outcomes will include estimation of relative attribute importance and trade-offs between implementation features. Preference heterogeneity by country and age group will also be explored. Quantitative surveys within the second workshops with adolescents will explore feasibility, acceptability, and appropriateness of the AfriCAT tool using validated scales [43]. For the qualitative components, outcomes will include identification of themes related to acceptability, feasibility, appropriateness, and alignment with stepped-care frameworks.

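### If a MODN candidate trained with overweighted positive cases is selected, its reported probabilities will be too high, and the plan states no correction

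*Protocol article*

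**What the plan says.** The MODN section of the protocol article describes a neural network that outputs diagnostic probabilities: "this approach models the evolving probability of specific diagnostic states, recalibrating predictions dynamically with each response". In that sentence the recalibration is the sequential update after each answer. It is not a correction for case weights.

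On training, the section states: "To remedy the low prevalence of internalizing disorders, we will also train models that overweight positive diagnosis cases". On selection: "The model achieving the best prediction performance using all the questions on the test set will then be selected". The performance measure used for selection is not named. For classification, Primary Outcomes says: "Diagnostic classification performance will be evaluated using established metrics such as sensitivity, specificity, and area under the receiver operating characteristic curve". Calibration appears under Secondary Outcomes: "For the MODN architecture, the calibration of probabilistic outputs will be assessed using calibration curves and the expected calibration error metric".

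The probabilities are a product of the study. Conceptual Framework gives the identification function as "estimating the probability of depressive and anxiety disorders and generating dimensional severity scores", and Prototype Development says of the provider interface: "The tool will be designed to generate dimensional severity estimates and probabilistic diagnostic outputs that can inform clinical decision-making".

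Neither the weight w nor the prevalence of any disorder is stated.

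**The concern.** A model trained with cases overweighted learns the probability of diagnosis in an artificial population with more cases than the one surveyed. That does no harm if only the ranking of adolescents is used. Here the probability itself is reported and its calibration is an outcome.

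Three features of the plan combine. It chooses a training method that shifts the output upward. It names metrics that cannot see the shift (AUC) or that may reward it (sensitivity at a fixed cut). It measures calibration without saying what follows if calibration is poor. A weighted candidate could therefore be selected and carried into the prototype with probabilities on the wrong scale.

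**Working it through.** The protocol gives no figure on this point, so there is none to reproduce.

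**Inputs from the protocol article.** N = 5155 (Data Source). The split is 80/20 and stratified on outcomes (Analysis), so 0.8 × 5155 = 4124 train and 0.2 × 5155 = 1031 test, and the test set keeps the sample prevalence. **Assumed:** w, prevalence and predictor effects.

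**Step 1. Size of the shift.** For adolescents with true probability p, the weighted log loss is −w·p·ln(q) − (1 − p)·ln(1 − q). It is smallest when q/(1 − q) = w·p/(1 − p), so

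q = w·p / (1 − p + w·p).

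For p = 0.05:
- w = 2: 0.10/1.05 = 0.095
- w = 5: 0.25/1.20 = 0.208
- w = 10: 0.50/1.45 = 0.345

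For p = 0.02 the same weights give 0.039, 0.093 and 0.169. Near the ends the absolute shift is small: at w = 10, p = 0.001 becomes 0.01/1.009 = 0.010. In the middle it is large: p = 0.20 becomes 2.0/2.8 = 0.714.

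**Step 2. Do the named metrics detect it?** Logistic models were fitted to simulated data with five independent standard normal predictors (coefficients 1, 0.8, 0.6, 0.4, 0.2), 4124 training and 1031 test records, and 100 replicates. The weight was w = (1 − prevalence)/prevalence, which balances the classes and is a high choice. ECE is the expected calibration error over 10 equal-width bins. Paired entries are unweighted / weighted.

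| Prevalence (w) | Mean prediction | Observed | ECE | AUC | Sensitivity at 0.5 | Specificity at 0.5 |
|---|---|---|---|---|---|---|
| 2% (49) | 0.020 / 0.324 | 0.020 | 0.007 / 0.304 | 0.841 / 0.840 | 0.018 / 0.748 | 1.000 / 0.762 |
| 5% (19) | 0.050 / 0.347 | 0.049 | 0.011 / 0.298 | 0.834 / 0.833 | 0.065 / 0.751 | 0.998 / 0.748 |
| 10% (9) | 0.100 / 0.370 | 0.099 | 0.017 / 0.271 | 0.826 / 0.826 | 0.154 / 0.751 | 0.990 / 0.741 |

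AUC does not move. Sensitivity at a fixed cut favours the weighted model, and ECE exposes it.

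**Step 3. Does a correction work?** Applying p = q/(q + w·(1 − q)), which subtracts ln(w) from the logit, returns ECE to 0.007, 0.011 and 0.018 and mean prediction to 0.020, 0.051 and 0.100.

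**Step 4. How much depends on the information available?** Here true logits were simulated at about 2.5% prevalence with w = 10, and the Step 1 shift was applied.
- AUC about 0.89: predicted/observed 5.3, ECE 0.106.
- AUC 0.997: 1.7 and 0.017.
- AUC 0.999: 1.3 and 0.007.

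A further illustration took a diagnosis fully determined by nine items (assumed prevalence 5.2%, w = 10). With all nine items ECE is 0.000. After five items predicted/observed is 1.9 (ECE 0.047), and after three items 2.6 (ECE 0.082). The item model is an assumption, so only the pattern should be relied on.

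**The case against.** The strongest reply has five parts.

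- **Weighted models are only additional candidates.** This stands. A reader might infer that every MODN probability will be inflated. The protocol does not support that, because unweighted models are trained as well.
- **The selection metric is unnamed, and log loss or Brier would penalise a weighted model.** This stands as far as it goes. AUC gives no systematic preference either way. But nothing in the named metrics guards against choosing a weighted model.
- **The planned calibration curves and ECE would reveal the inflation.** This largely stands, since the test set keeps the sample prevalence. But calibration is not named as a selection criterion, and no remedy is stated. Selection uses all questions, where DISC-5 diagnoses are scored from the same interview, so full-bank probabilities probably lie near 0 or 1. A check made there can look good while outputs after early stopping do not.
- **Large inflation factors rest on assumed w and moderate discrimination.** This stands. A reader might infer many-fold overstatement, but Step 4 shows that the ratio can be as low as 1.3 with near-complete information. The fall in specificity at a 0.5 cut is also paired with a large gain in sensitivity, which is what the overweighting is meant to achieve.
- **The prototypes are for research only.** This stands. A reader might infer that unaffected adolescents will be sent to scarce services. Prototype Development and Ethical Considerations rule out clinical deployment in this phase, and Study Design places external validation before broader implementation.

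A reader might also infer that question selection and stopping will be distorted. The MODN section names entropy only for the comparison baseline and DISC-5 criteria for the baseline stopping rule. The effect would arise only if a chosen rule used the predicted probability.

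**Conclusion.** The concern holds in a conditional form. MODN candidates trained with positive cases overweighted by w output odds inflated by about w relative to the surveyed population. If one is selected, the reported probabilities will be too high, and the plan states no correction. This is more than detail left out of a condensed article: a stated training choice biases a stated output, and the stated metrics do not protect against it.

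The direction holds for any w above 1. The size is not fixed by the documents. It ranges from little, where probabilities are near 0 or 1, to a two- to seven-fold rise at a true 0.05 for w between 2 and 10 (0.095/0.05 = 1.9; 0.345/0.05 = 6.9). The formula is exact for a well-specified log-loss fit and approximate for an early-stopped network. The change should be made, but it does not undermine the study.

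**What to change.** In the MODN section, state that:

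1. Outputs of any case-weighted model will be recalibrated before selection and evaluation, preferably by a recalibration fitted within the training folds. The ln(w) logit offset is a simple alternative, but only approximate for an early-stopped network.
2. Model selection will include a proper score (log loss or Brier) computed after recalibration.
3. Calibration intercept, slope and ECE will be reported at the adaptive stopping point as well as with all questions answered.

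The cost is a few sentences and a little extra analysis. The ln(w) correction leaves ranking and AUC unchanged. The Results section reports MODN development as still in progress, so the change can be made before selection.

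If the purpose of overweighting is only to raise sensitivity, moving the cut on an unweighted model is an alternative that leaves its probabilities on the population scale.
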